Reliable analyses by hormone type require large numbers of exposed cases, as well as detailed prospective information on prescribing. The GPRD has both, and sufficient information to allow adjustment or stratification by known potential confounders such as body mass index and alcohol use (as well as some less well-established risk factors for breast cancer such as smoking and use of aspirin).

Finally, a major source of evidence on the effects of exogenous sex hormones on breast cancer risk has been, and will continue to be, the results from pooled reanalyses of individual data included in the international Collaborative Group on Hormonal Factors in Breast Cancer mentioned above. The proposers of the current study also run this collaboration; collaborative results are currently being updated for both hormonal contraceptives and for hormone therapy for the menopause, and a comprehensive and up to date analysis of GPRD data would allow the optimal contribution from GPRD to the worldwide evidence.

Study type

Hypothesis testing and confirmation of findings of public health significance.

Study design

Nested case-control study within defined cohort in GPRD, using cases and controls matched for age, practice and observation time in the GPRD. 2 controls will be selected per case to maximise study power.

Study population

Women aged 20-79 years registered with GPRD on or after 1 January 1995.

Inclusion criteria:

- Age 20-79 [age group includes almost all cancers and hormone prescriptions]
- Registered with GPRD up –to-standard practice on or after 1 January 1995
- Fulfilling GPRD acceptable patient criteria
- At least 1 year in GPRD before index date (date of diagnosis of case)

Exclusion criteria:

- Previous invasive or *in situ* breast cancer

Case selection

Cases will be identified as any eligible patient with an incident diagnosis of invasive or *in situ* cancer of the breast between 1 January 1995 and latest available date.

Selection of comparison group (controls)

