2 controls per case selected from eligible patients who do not have a medical diagnosis of breast cancer documented at any time up to the latest available date (above). This includes diagnoses of breast cancer prior to or during the study period. Controls and cases matched on age (within 2 years), practice and observation time in GPRD (ie controls to have observation time in GPRD at least as long as their matched case, to allow exact matching in the analysis; for cases, start date of observation = most recent of patient registration date, practice up-to-standard date and practice management start date, end date (index date) = date of diagnosis). Index date for controls defined as the diagnosis date of their matched case.

Sample size and power calculations

Incidence of invasive breast cancer in GPRD is similar to that in the general UK population, which is ~63 per 100,000 per year (Office for National Statistics (ONS), 2007) ie 630 cases per million person years. There are currently 62 million person years of research acceptable followup in GPRD (GPRD Gold October 2010 release), so we might expect some 39,000 incident breast cancers in the whole database, and of these about 20,000 will be in women aged 50-75 (ONS, 2007). It seems reasonable to assume, allowing for some restriction of age group and observation time, that our analyses would include at least 10,000 breast cancer cases and 40,000 controls. These numbers are consistent with those in the GPRD study by Opatrny et al, which included incident cases of invasive breast cancer in women aged 50-75 diagnosed between 1998 and 2004, and had over 6,000 cases [14]. From the Opatrny study and from our previous analyses in GPRD (protocol no. 10_006; analyses not yet published) the prevalence of HT prescribing in women over 40 years will be approximately 33 % (possibly lower in very recent years); OC prescribing in women 20-50 years is estimated at about 20 % in GPRD in recent studies of outcomes other than cancer [16].

With these numbers the study will be amply powered with 80% power and 95% confidence to detect a minimum relative risk of <1.1 in relation to overall risk for HT or OC use v no use, and of <=1.5 for any subgroup with exposure prevalence of 1% or more.

Exposures, outcomes, covariates

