Exposure: patients will be considered exposed to exogenous hormones if they have at least one prescription for a hormonal contraceptive or hormone replacement therapy preparation (as defined in the British National Formulary (BNF)) within the observation period (start of follow-up to index date). Sensitivity analyses will be performed restricting the definition of exposure to those with 2 or more prescriptions. OC/HT type will be assigned based on BNF classification, classing women with separate prescriptions on the same day for oestrogen and progestagen as being prescribed combined oestrogen-progestagen therapy.

Outcomes: incident invasive and *in situ* cancers of the breast (ICD-10 C50 and D05)

Covariates: smoking status, alcohol drinking [most recent record before index date], body mass index [most recent record at least 2 years before index date, to account for reverse causality] and parity will be taken into account where possible in adjusted and/or stratified analyses. Availability of prescription data will allow medications such as aspirin and bisphosphonates, which may be related to breast cancer risk and to hormone use, to be considered in supplementary analyses.

Data/statistical analysis outline methodology

Conditional logistic regression will be used to estimate crude and adjusted odds ratios (relative risks) with 95% confidence intervals for cancer risk in relation to hormone prescription vs no prescription within the observation period. Analyses for hormonal contraceptives will include hormone type and mode of delivery, including progestagen-only contraception; for HT, hormone type, mode of delivery and timing of use; for both, the risks associated with use of Mirena will be examined. Adjustment variables will include smoking status (never, current, past, unknown), alcohol drinking (none, some, unknown) and body mass index (<25, 25-30, 30+ kg/m sq, unknown) and where possible, parity (at least nulliparous, parous, unknown). Data analysis will be carried out using STATA software v10. Analyses for HT will generally be restricted to women aged over 40, and for OC use to women aged 20-50 years.

Patient/user group involvement

None

Limitations of study design, data sources, analytic methods

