Validation studies have shown GPRD outcome and exposure (prescription) data to be sufficiently reliable and complete for epidemiological analysis; and the GPRD population is sufficiently representative of the UK population for the results to be broadly generalisable.

Potential limitations of the GPRD for these analyses include the lack of complete information on smoking, alcohol and body mass index, and particularly on reproductive factors such as parity, breastfeeding history and age at first birth; and the fact that information on prescribing of hormonal contraceptives is likely to be incomplete, as prescriptions issued outside general practice will not always be recorded. It is estimated that 80% of all prescriptions for hormonal contraceptives in the UK are issued in general practice (UK Family Planning Organisation, personal communication). Data on other potential confounders, such as diet and socioeconomic status, are not available (the impact of the latter will to some extent be minimised by matching of cases and controls by GP practice).

Such missing data will have the effect of diluting the study power, but should not introduce bias unless data is missing for reasons related to the outcome. The consistency of the results of previous HT studies in GPRD with those from studies in which reproductive factors were taken into account argues against substantial bias in the database; similar comparisons will help in interpreting results on hormonal contraceptive use. Sensitivity analyses with restriction to patients with full data on adjustment variables (complete case analysis) will be performed to test the effect of missing data in the main analyses.

Use of other prescribed drugs which may affect breast cancer risk (eg bisphosphonates, NSAIDs) cannot readily be taken into account by adjustment as there are complex possible relationships between prescribing of these drugs and of HT. Stratified analyses will allow these factors to be taken into account to some extent.

Plans for communicating and disseminating results

We aim to publish the results of this study in a peer-reviewed journal at the earliest opportunity. Study results will also be submitted for presentation at an appropriate scientific meeting. There are no restrictions on the extent or timing of publication.

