**Revised definitions of cases and controls**

In keeping with the above protocol, the revised definitions for cases and controls are outlined as follows. All women are required to have a minimum of 12 months up-to-standard data in the CPRD prior to index date (date of diagnosis for the case) to be eligible for study inclusion.

Case definition

Cases are defined as all female participants of the CPRD with incident diagnosis of invasive or in situ breast cancer documented between 1^st^ January 1995 and 2017 (to most recent data available), and aged 20- 79 years of age at index diagnosis. Women are excluded if they have a past history of invasive or in situ breast cancer.

The list of Read codes used to flag women with incident breast cancer diagnosis as per previous protocol is shown Appendix 1.

Control definition

Controls are defined as all women without a medical diagnosis of breast cancer documented (up to last date of data extraction for 2017). This includes any diagnoses for breast cancer prior to 1^st^ Jan 1995 and during the study period from 1^st^ Jan 1995 to 2017. Cases are therefore not eligible to act as controls in this study.

Controls will be matched in a 2:1 ratio to cases based on:

- Year of birth(+/- 2 years)
- Same general practice
- Similar period of observation as the case.

The period of observation in CPRD for controls must include the full observation time (regstart to index diagnosis) for cases, so that observation periods may be matched exactly for the purpose of analyses.

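### Hormone prescriptions count as exposure right up to diagnosis, with no lagged analysis, although the same section lags BMI by 2 years against reverse causality

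*Protocol*

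**What the plan says.** All references are to the protocol.

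- **Exposure** (Exposures, outcomes, covariates): one hormonal contraceptive or HT prescription suffices if it falls "within the observation period (start of follow-up to index date").
- **End of that window** (Selection of comparison group): for cases, "end date (index date) = date of diagnosis". Controls take the diagnosis date of their matched case.
- **Sensitivity analysis on exposure** (Exposures, outcomes, covariates): "Sensitivity analyses will be performed restricting the definition of exposure to those with 2 or more prescriptions". No other variation of the exposure definition is named.
- **BMI** (same section): "body mass index [most recent record at least 2 years before index date, to account for reverse causality".
- **Look-back** (Study population): "At least 1 year in GPRD before index date (date of diagnosis of case"). The 2017 amendment, under Revised definitions of cases and controls, keeps this as a "minimum of 12 months up-to-standard data in the CPRD prior to index date".
- **Missing BMI**: the model uses "body mass index (<25, 25-30, 30+ kg/m sq, unknown") (Data/statistical analysis outline methodology). The Limitations section adds "Sensitivity analyses with restriction to patients with full data on adjustment variables (complete case analysis").

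**The concern.** The protocol recognises that a measurement close to diagnosis may be affected by the cancer or its work-up, and protects a covariate against this. It gives the main exposure no such protection, not even in a sensitivity analysis. A consultation that starts hormones can also lead to a breast examination, and breast symptoms can influence whether hormones are started. A first prescription in the last months may then be associated with the diagnosis without contributing to it.

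The study looks for small effects: a detectable relative risk below 1.1 overall, and about 1.3 for current oral contraceptive use according to the Background. A distortion of a few hundredths in the odds ratio is not negligible on that scale, and more cases and controls would not shrink it. The Limitations section does not mention it.

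A secondary mismatch sits beside this one. Eligibility needs 1 year of data, while a usable BMI must be at least 2 years old.

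**Working it through.** **1. The plan's own figure.** Inputs from Sample size and power calculations: 10,000 cases, 40,000 controls, exposure prevalence 33% (HT), 20% (OC) and 1% (subgroup), 80% power, 95% confidence (taken as two-sided alpha 0.05). With p0 the prevalence in controls, the prevalence in cases is p1 = p0·OR / (1 + p0·(OR − 1)). The power is that of an unmatched comparison of two proportions, solved for the OR that gives 80%.

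| Cases : controls | 33% | 20% | 1% |
|---|---|---|---|
| 10,000 : 40,000 | 1.068 | 1.080 | 1.335 |
| 10,000 : 20,000 (the 2:1 design) | 1.075 | 1.088 | 1.372 |
| 33,000 : 66,000 (first extraction, per the amendment) | 1.041 | 1.048 | 1.198 |

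The stated limits (below 1.1, and at most 1.5) reproduce. The last row is a best case, since the HT and OC analyses are restricted by age.

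**2. What the exposure rule lets in.** The window closes on the date of diagnosis, so a first prescription days earlier makes a woman exposed. Two prescriptions within the last few months satisfy the stricter definition as well. That analysis drops isolated late prescriptions but leaves the period itself in.

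**3. Size, on stated assumptions.** Controls are counted up to the same date, so late first prescriptions that are equally common in cases and controls create no spurious association. What matters is an excess e among cases. With a true OR of 1, the observed OR is [(p0 + e)/(1 − p0 − e)] / [p0/(1 − p0)]. For example, at p0 = 0.33 and e = 0.01: (0.34/0.66)/(0.33/0.67) = 1.046. The values of e are assumptions; the documents give none.

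| Prevalence | e = 0.5 points | e = 1 point | e = 2 points |
|---|---|---|---|
| 33% | 1.023 | 1.046 | 1.093 |
| 20% | 1.031 | 1.063 | 1.128 |
| 1% | 1.508 | 2.020 | 3.062 |

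In the 1% row, e = 0.5 points already means half as many extra users as there are users among controls, so the right-hand cells are extreme.

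Turned round, the excess that would by itself produce the protocol's own target is p1 − p0:

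- 33%, OR 1.1: 0.363/1.033 − 0.33 = 0.021
- 20%, OR 1.1: 0.22/1.02 − 0.20 = 0.016
- 1%, OR 1.5: 0.015/1.005 − 0.01 = 0.005

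If breast symptoms deter starting, e is negative and the odds ratio is pulled down. The direction is not known in advance.

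**4. BMI.** With observation of 1 to under 2 years, no observed time lies 2 or more years before the index date (at the minimum, 1 − 2 = −1 year). Only a record from before the observation period could qualify. The protocol confines prescriptions to that period but is silent on this for BMI. The choice has consequences:

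- If only records in the matched window count, BMI is unknown for every member of such a set. The term is constant within the set and cancels from the conditional likelihood. The set still informs the hormone odds ratio, without BMI adjustment, and it leaves the complete-case analysis.
- If older records count, controls may have longer histories than their case, because their observation need only be at least as long. Missing BMI could then differ by case status, which is the condition under which the Limitations section itself expects bias.

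**The case against.** The strongest reply is that recent use is a target of the study. The Background is about current users, and the objective covers timing of use, so a lag in the main analysis would discard part of the question. That stands, and it is why the lag belongs in a sensitivity analysis.

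The mechanism is also narrower than it may look. Under an ever-prescribed definition, stopping hormones because of symptoms cannot make an exposed woman unexposed. A late prescription changes status only for a woman with no earlier one in her window; continuing users are unaffected. Both points are right. They limit the size of the effect without removing it.

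It can be said that a lagged analysis is detail for an analysis plan that is not shown. But the protocol itself fixes the exposure window and names the sensitivity analysis on it, so the gap lies in a rule stated here.

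On BMI, a reader might infer that the look-back makes the lagged BMI unobtainable and adjustment absent by design. The documents do not support this. BMI records are not restricted to the observation period. That period can start late because of practice dates in a woman registered for years. An unknown category and a complete-case analysis are already planned. If only records in the matched window are used, the structural gap falls alike on a case and her controls.

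**Conclusion.** The exposure point holds. Prescriptions count up to diagnosis, the section's reverse-causality safeguard covers BMI only, and the analysis requiring two or more prescriptions is no substitute for a lag. The size is not known from the documents. An excess of about 2.1 percentage points of late first prescriptions among cases at 33% prevalence, or 1.6 at 20%, would by itself give an odds ratio of 1.1. These figures assume a true odds ratio of 1 and use unmatched arithmetic.

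Two stronger readings are not supported. Nothing shows that prescriptions in the final months are generally a result of the disease process, so the main estimate cannot be called biased; it is untested on this point. Nor can the share of sets lacking a lagged BMI be stated. An exponential observation time with a mean of 5, 7 or 10 years would put 1 − exp(−1/mean) = 18%, 13% or 10% of eligible sets at 1 to 2 years, but both the shape and the means are assumptions. Even then the result would be a ceiling on BMI made missing by this rule. What remains on BMI is an unstated rule that needs one sentence. The stated power is unaffected.

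**What to change.** 1. Keep the main analysis. Add a sensitivity analysis that ignores hormone prescriptions in the 12 months before the index date, for cases and controls alike, in matched sets with at least 2 years of observation. Name the period just before diagnosis in the Limitations section.
2. State whether BMI records from before the observation period are used, and apply the same rule to cases and controls. Restricting the main adjusted analysis to sets with 2 or more years of observation is not required.

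The cost is one further run on data already requested, with fewer sets and a somewhat lower exposure prevalence in that run only. As an illustration on assumed inputs, 8,000 cases at 25% prevalence give a minimum detectable relative risk of 1.083 (4:1) or 1.092 (2:1). At 20% it is 1.090 or 1.099, and at 15% it is 1.101 or 1.111. The 33,000 cases reported in the amendment suggest there is room for this loss.

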Breast cancer is strongly influenced by female sex hormones such as oestrogen and progesterone; both by those produced naturally in a woman's body (endogenous hormones), and by hormones taken for contraception or as hormone therapy for the menopause (HT) (exogenous hormones). Current users of both hormonal contraceptives and HT have an increased risk of breast cancer, up to 2-fold in the case of HT preparations containing both oestrogen and a progestagen (synthetic progesterone). Understanding these risks has direct implications for public health: for example, rates of breast cancer have fallen in response to falls in prescribing of HT, following publication of reliable evidence on breast cancer risk in recent years. There are however some gaps in our knowledge. It has been suggested that the effect of HT on breast cancer risk may depend on the timing of use (in relation to age or menopausal status); and there is limited information on the risks associated with progestagen-only contraceptives, or with specific contraceptive formulations. The GPRD's large size and the availability of detailed prescription data by type will allow us to examine these questions; our analyses would extend and supplement previous GPRD studies of hormone use and breast cancer.

Objectives, specific aims and rationale

*Research objective:* to obtain relative risks for incident breast cancer in relation to prior prescribing of contraceptive hormones and of hormone replacement therapy for the menopause (HT), by type and timing of use.

*Specific aims:* to add to existing knowledge about the effect of use of exogenous female sex hormones on risk of breast cancer, examining unanswered questions including the influence on risk of the timing of HT use, and suggested differences in risk associated with specific contraceptive preparations.

*Rationale:* current use of both HT and contraceptive hormones has been shown to increase risk of breast cancer, and this knowledge has direct public health implications. The large size and reliable prescribing information in the GPRD will allow us to add to existing knowledge by examining breast cancer risk in relation to specific hormone preparations and to timing of HT use, where there is at present suggestive but unconfirmed evidence for differences in risk.

Background

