The development of breast cancer in women is strongly influenced by female sex hormones, and the risks associated with reproductive patterns (parity, age at first birth) and with use of oral contraceptives and of hormone therapy for the menopause have been extensively described [1-6]. However, unanswered questions remain. For hormonal contraceptives, there is good evidence for a modest increase in risk of breast cancer in current users of oral contraceptives containing both oestrogen and progestagen, both for older [4] and more recent [7] preparations, with relative risks for current compared with never use of around 1.3. There may be higher risks associated with specific formulations and modes of delivery, such as triphasic pills containing levonorgestrel [7], but evidence is limited. Similarly the risks associated with use of progestagen-only contraceptives, including the intra-uterine device Mirena, are not clear [4].

Some types at least of hormone therapy for the menopause are known to be associated with increased risk of breast cancer, with relative risks of about 2 reported for current use of combined oestrogen-progestagen preparations [8]. It has recently been suggested that the effect of HT use on breast cancer risk may vary depending on women's age and/or menopausal status when use starts, with risk higher for use starting around the time of the menopause than for later use [9]. Such findings have important potential implications for clinical practice and need to be investigated in independent datasets. There is debate too about the relative risks associated with different formulations of HT, including, again, the use of Mirena progestagen-releasing intrauterine devices [10]; as well as differences by mode of drug delivery (transdermal vs oral) [11].

We are not aware of previous research studies in the GPRD examining cancer risk in relation to use of hormonal contraceptives. For HT, five previous publications have described analyses of HT use and risk of breast cancer from the GPRD [12-15]. The most comprehensive, with 6,347 cases aged 50-75 [14], used data up to 2004; the most recent (1261 cases with data to 2007) focussed on risk associated with a specific progestagen, dydrogesterone [15]. Our proposal would allow updating and extension of the previous analyses to 2010, to include all HT types, including Mirena, and to examine risk by timing of use.

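### Women whose only hormone use came before the observation period are counted as unexposed, so the odds ratios are not against never use and are biased towards 1 if any excess risk outlasts stopping

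*Protocol*

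**What the plan says.** The Protocol's exposures section counts a woman as exposed if she has at least one hormone prescription between start of follow-up and index date. The analysis section then estimates odds ratios "for cancer risk in relation to hormone prescription vs no prescription within the observation period".

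The section on selecting controls fixes when that period opens: "start date of observation = most recent of patient registration date, practice up-to-standard date and practice management start date". The study population section asks for at least one year before index date, and the 2017 amendment (Revised definitions of cases and controls) repeats this as a "minimum of 12 months up-to-standard data in the CPRD prior to index date". HT analyses generally cover women over 40 and contraceptive analyses women aged 20 to 50.

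Other parts of the Protocol describe the comparison differently:

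- The power section claims ability "to detect a minimum relative risk of <1.1 in relation to overall risk for HT or OC use v no use".
- The Background cites combined oral contraceptives "with relative risks for current compared with never use of around 1.3".
- For HT, the Background cites "relative risks of about 2 reported for current use of combined oestrogen-progestagen preparations" and names no reference group.

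The limitations section names one source of incomplete hormone data: contraceptive prescriptions issued outside general practice. It says that missing data of the kinds it lists reduce power but cause no bias unless the missingness is related to outcome.

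**The concern.** A woman of 48 who took contraceptives for years, changed practice 13 months before her index date and has had no prescription since is in the reference group. Nothing in the plan separates her from a woman who never used hormones.

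- The sensitivity analysis requiring two or more prescriptions changes only who counts as exposed.
- The complete-case analysis concerns the adjustment variables.
- Matching on observation time makes the cut-off the same for a case and her controls, but it does not take earlier users out of the reference group.

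The interpretation of the result is at stake. The limitations section plans to interpret the contraceptive findings by comparison with other studies, and the Background intends the data for an international pooled reanalysis. Both uses need to know what the reference group is. The limitations section, as written, would lead a reader to expect a loss of precision where the estimate itself may be shifted.

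**Working it through.** **1. The plan's own power figure.** Inputs from the power section: 10,000 cases, 40,000 controls, 80% power, 95% confidence (taken as two-sided 5%), and control exposure p0 of 33% (HT), 20% (contraceptives) or 1% (subgroup). Case exposure is p1 = OR·p0 / (1 + p0(OR − 1)). An unmatched two-proportion normal approximation is solved for the OR that gives 80% power. The design section specifies two controls per case, so both ratios are shown.

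| Control exposure | 4:1 | 2:1 | Stated |
|---|---|---|---|
| 33% | 1.068 | 1.075 | <1.1 |
| 20% | 1.080 | 1.088 | <1.1 |
| 1% | 1.335 | 1.372 | ≤1.5 |

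The stated figures hold for prescription against no prescription in the window. (The mismatch between 40,000 controls and a 2:1 design is a separate matter.)

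**2. What earlier users in the reference group do.** Let c be the share of the reference group among controls with use only before the window, RRpast their relative risk against never use, and RR that of the exposed. The average risk in the reference group is (1 − c) + c·RRpast, so

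observed OR = RR / (1 + c(RRpast − 1)).

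The documents give neither c nor RRpast; both are assumptions here.

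| RR against never use | RRpast | c | Observed OR |
|---|---|---|---|
| 1.3 | 1.00 (none persists) | any | 1.30 |
| 1.3 | 1.15 (half) | 20% | 1.3/1.03 = 1.26 |
| 1.3 | 1.15 (half) | 50% | 1.3/1.075 = 1.21 |
| 1.3 | 1.30 (all) | 20% | 1.3/1.06 = 1.23 |
| 1.3 | 1.30 (all) | 50% | 1.3/1.15 = 1.13 |
| 2.0 | 1.50 (half) | 10% | 2.0/1.05 = 1.90 |
| 2.0 | 1.50 (half) | 30% | 2.0/1.15 = 1.74 |

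The values 1.3 and 2.0 are literature figures for current use. The planned exposed group is anyone with a prescription in the window. The table therefore shows direction and rough size and does not predict this study's results. For HT, 2.0 is treated as a never-use figure by assumption.

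**3. Equal misclassification still biases.** Take 10,000 controls at the plan's 20% contraceptive exposure: 2,000 exposed and 8,000 reference. With c = 20%, the reference group holds 1,600 earlier users and 6,400 never users. Let all users carry 1.3. Cases then occur in proportion 2,600 (exposed), 2,080 (earlier) and 6,400 (never).

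- Share of users missed among controls: 1,600/3,600 = 44.4%.
- Share of users missed among cases: 2,080/4,680 = 44.4%.
- Observed OR: (2,600/8,480) / (2,000/8,000) = 1.23, not 1.30.

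The missingness among users is identical in cases and controls, and the odds ratio still moves. The statement in the limitations section is therefore not correct for exposure data.

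**4. How much a window can cover.** At age 50, windows of 1, 5 and 10 years cover 1/30, 5/30 and 10/30 (3%, 17% and 33%) of ages 20 to 50. At age 30, 5 and 10 years cover 50% and 100% of ages 20 to 30. Coverage depends heavily on age, and even a 10-year window is partial for older women.

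**The case against.** The strongest reply is that the plan is more consistent than it looks. The objective is "to obtain relative risks for incident breast cancer in relation to prior prescribing of contraceptive hormones" and of HT, and it names no never-use comparator. The power inputs are prescribing prevalences, so use against no use can be read as shorthand for prescribed against not prescribed. The figure of 1.3 is background literature and not a design target. All of this stands: the aims are not contradicted, and the detectable relative risks need no change on this point.

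A reader might go further and infer that the study loses its power. If 1.1 is read as an effect against never use, with full risk in past users and c = 30%, power at 10,000 cases and 2:1 falls from 96% to 72% (HT) and from 89% to 59% (contraceptives). That needs a reading of 1.1 which the document does not state and two assumed inputs. With the 33,000 cases and 66,000 controls reported in the amendment, the same scenario gives about 98% power or more if all sets were analysed, though age-restricted counts are not given.

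A reader might also infer that comparisons between hormone types are distorted. Types compared within the same sets share one reference group, so the denominator in the formula cancels in the ratio of their odds ratios. Distortion would require types to differ in window length, which the documents do not show.

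Finally, the analysis section is an outline, a fuller plan may exist, and the power section mentions some restriction of observation time without a figure. That excuses missing detail. It does not excuse a reference group that the Protocol itself fixes, or an incorrect statement about bias.

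**Conclusion.** The point holds in a conditional form. The reference group is women with no prescription recorded in a window that may last only a year. It contains an unknown share of earlier users, and no planned analysis addresses this. The odds ratios are biased towards 1 only if earlier use carries residual excess risk in the same direction; with none, they do not change. It would be wrong to say that bias is certain.

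With half the excess persisting and 20% to 50% of the reference group affected, 1.3 would be seen as about 1.26 to 1.21. That is modest, but more cases will not reduce it. The size rests wholly on assumed values. What does not depend on them is the mismatch in labels and the error in the limitations section, which treats equal exposure misclassification as harmless to the estimate. This is worth correcting; it does not undermine the design.

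**What to change.** (a) In the analysis section, add a sensitivity analysis of the main HT and contraceptive odds ratios by length of the matched observation period (for example 1–4, 5–9 and 10+ years), or with a longer minimum look-back. Each matched set shares one window, so sets stay intact. Adjust for or display age and calendar period, because window length may track both. Present the longest-window estimate as less contaminated, not as an estimate against never use.

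(b) In the power section, relabel the contrast as prescription versus no prescription recorded in the observation period. Leave the detectable relative risks as they are on this point.

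(c) In the limitations section, name use before the window as a limitation, and correct the statement on bias so that it does not extend to exposure data.

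A separate class for women with earlier use only is optional. It is sound only if pre-window records are available on the same basis for cases and controls, and the documents do not show that such records were extracted.

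The cost is a few lines of text and some stratified models on the planned dataset. The downside is wider intervals in the long-window stratum.
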